#### Recruitment strategies

Several strategies will be applied to participant recruitment. In this RCT, we will recruit mainly participants who are hospitalized patients at acupuncture departments and neurology departments in Shanghai Shuguang Hospital. We will put up posters in the hospitals and advertisements across WeChat (a Chinese multipurpose social media mobile application software), which will give brief descriptions of the population needed to be enrolled (with 62 being the goal population for this trial); the free acupuncture treatments offered to participants; the purpose, procedures, treatments, and possible risks of the trial; and the contact information of the researchers. After the screening test, all of the participants will be required to sign the consent forms and assigned to different intervention groups by another researcher afterward. Clinical recruitment staff will be responsible for the recruitment process.

### Randomization and allocation

The block randomization method will be used by a specified researcher who is not involved in the trial. Randomization is planned to be conducted by using IBM SPSS Statistics version 24.0 software (IBM, Armonk, NY, USA) to generate a random number table that allocates the eligible participants to either of two groups (the EA group and the sham EA group) in a 1:1 ratio after they have signed printed informed consent forms. The random allocation cards will be made and sealed in opaque envelopes. Patients will be assigned into different groups by another researcher who is also responsible for informing the acupuncturists of the group allocation.

### Blinding

Because this is a single-blind study, participants, outcome assessors, and data statisticians will be blinded to the group allocation. However, acupuncturists will not be blinded, because sham acupuncture is definitely practiced differently from real acupuncture. Each participant will be assigned to receive EA treatment at different times in separate treatment rooms to avoid communication, and acupuncturists will have been trained previously not to inform other researchers, including outcome assessors and data statisticians as well as the participants, about group allocation information. Blinding will be maintained during the whole study process. James et al.’s blinding index will be evaluated after the completion of the study to evaluate the success of blinding [20].

### Interventions

All the eligible participants will be randomized into one of two groups: the EA group or the sham EA group. The EA treatment, consisting of 12 sessions across 4 weeks with 3 sessions each week, will be performed by experienced acupuncturists to ensure identical acupuncture treatment according to standard operating procedures. The participants in both groups will receive treatment by acupuncturists at the same acupoints as follows: Baihui (DU20), Sishencong (EX-HN1), Ganshu (BL18), Sanyinjiao (SP6), and Taichong (LR3), all of which are the most frequently used acupoints for treating PSD according to previous research. The needle retention time in both groups is 30 minutes. In addition to EA treatment, the participants will receive basic Western medical therapy for stroke (Table 1).

**Table 1 Tab1:** Intervention details of both groups

	EA group	Sham EA group
Acupoints	DU20, EX-HN1 BL18, SP6, LR3	DU20, EX-HN1 BL18, SP6, LR3
Needle penetration	DU20, EX-HN1: 10 mm BL18, SP6, LR3: 15 mm	No needle penetration
Needle stimulation	De-qi sensation	No de-qi sensation
Electrostimulation	Current frequency: 2/100 Hz	No electrostimulation
Needle retention time	30 minutes	30 minutes
Treatment tools	Stainless steel needles and a PG-306 electroacupuncture device	A Park Sham Device with a PG-306 electric pulse generator with a cut wire inside
Treatment frequency and duration	Three sessions per week, 4 weeks	Three sessions per week, 4 weeks

*Abbreviations: BL18* Ganshu, *DU20* Baihui, *EA*, Electroacupuncture, *EX-HN1* Sishencong, *LR3* Taichong, *SP6* Sanyinjiao

#### Electroacupuncture group

Stainless steel needles and a PG-306 EA device will be used in treating with participants in the EA group. Acupuncturists will sterilize participants’ skin and then puncture DU20 and EX-HN1 horizontally 10 mm into the scalp skin. SP6 and LR3 will be punctured vertically 15 mm into the skin, and BL18 will be punctured obliquely 15 mm into the skin. Needling sensation (De-qi sensation) will be obtained through needle manipulation, including lifting, thrusting, and rotating. The needles will be stimulated using an electric current at a frequency of 2/100 Hz with a PG-306 EA device for about 30 minutes per EA treatment session.

#### Sham electroacupuncture group

A Park Sham Device with blunted needles that do not penetrate the skin, as described previously [21–23], will be applied to the participants in the sham EA group. The sham device, installed with a PG-306 electric pulse generator with a cut wire inside, will give only a little stimulation but a fake sound resembling the electrostimulation. Thus, there is no needle penetration and no electric current stimulation through the use of the Park Sham Device.

### Outcomes

An independent researcher who is blinded to the group allocation will be in charge of the outcome assessment.

#### Primary outcome

The changes in HRSD scores between baseline, 2 weeks after EA treatment onset, 4 weeks after treatment onset, and at 8-week follow-up will be set as the primary outcome of the clinical study.

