### Sample size

According to the difference of HRSD scores between the two groups, the required sample size of each group will be carefully calculated by the data statistician. Based on our previous pilot study, the change in the SD of HRSD scores in the sham EA group is 5 points and that in the EA group is 13 points. If the HRSD score change in the EA group is 8.5 points higher than that in the sham EA group, it will be considered clinically significant. On the basis of a 5% false-positive error rate (α = 0.05, two-sided) and 80% power (β = 0.2), the sample size is estimated as follows:$$ {\displaystyle \begin{array}{l}n=\frac{{\left({Z}_{1-\alpha }+{Z}_{1-\beta}\right)}^2\times \left({\sigma}_1^2+{\sigma}_2^2\right)}{\delta^2}\\ {}\kern1.5em =\frac{{\left(1.96+1.28\right)}^2\times \left({5}^2+{13}^2\right)}{8.5^2}\approx 28.48\end{array}} $$

A sample size of at least 29 participants should be recruited in each group. Assuming about a 10% dropout rate, which has been verified in the pilot study, a total of 62 participants will be enrolled in the trial.

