### Statistical analysis

An independent statistician will use IBM SPSS Statistics 24.0 software to conduct the whole data analysis. According to the intention-to-treat (ITT) principle, both ITT and per-protocol (PP) analyses will be performed. Any participant who receives treatment more than nine times during the study will be enrolled in the PP analysis. In terms of ITT analysis of secondary outcomes, the last observation carried forward rule will be used as the strategy in management of missing data. For the primary outcome, the maximum likelihood estimation method will be used.

All continuous variables will be presented as mean ± SD, and categorical variables will be presented as number (percent). The statistical significance level is considered to be 0.05 (two-sided) with 95% CIs. The homogeneity of the baseline characteristics between the two groups is designed to be tested by the two-sample *t* test for quantitative data and the chi-square test for qualitative data. If there is a possibility of covariance, analysis of covariance (ANCOVA) will be used for adjustment of baseline characteristics. To compare variables between the two groups, the parametric two-sample *t* test for normally distributed data and the nonparametric Mann-Whitney *U* test for nonnormally distributed data will be used. Repeated-measures ANCOVA will be applied to analyze different time point assessments between groups and interaction between groups and observed time. Differences within groups will be assessed with the paired *t* test (parametric method) and the Wilcoxon signed-rank test (nonparametric method).

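### The primary outcome covers HRSD change at three post-baseline visits, and no deciding visit, contrast or test is named, so the 5% error used for sizing attaches to no defined comparison

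*Protocol article*

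**What the plan says.** The Primary outcome section of the protocol article gives the primary outcome as "The changes in HRSD scores between baseline, 2 weeks after EA treatment onset, 4 weeks after treatment onset, and at 8-week follow-up". All three post-baseline assessments sit on the same level.

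The Sample size section works from a single two-group comparison. Its effect is introduced with "If the HRSD score change in the EA group is 8.5 points higher than that in the sham EA group", and no visit is attached. The pilot SDs of the change are given as "in the sham EA group is 5 points and that in the EA group is 13 points", again without a visit. Alpha is 5% two-sided and the stated power is 80%. The result is "A sample size of at least 29 participants should be recruited in each group", and 62 in total after dropout.

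The Statistical analysis section sets one general level: "The statistical significance level is considered to be 0.05 (two-sided) with 95% CIs". It then lists two-sample t or Mann-Whitney tests between groups, ANCOVA where baseline adjustment seems needed, and a repeated-measures ANCOVA that yields both a group comparison and a group-by-time interaction. The only statement particular to the primary outcome is that missing data are handled by maximum likelihood. That statement names no visit and no contrast.

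The Hypotheses section mentions 12 sessions over 4 weeks in its first hypothesis, which is about improvement under EA. The second hypothesis, which compares EA with sham, names no time.

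**The concern.** A confirmatory 5% error rate belongs to a defined comparison. Here the reader cannot tell which comparison decides the trial: week 2, week 4, the 8-week follow-up, an average over visits, or the interaction. A difference that appears at week 2 and fades, and one that appears only at follow-up, could each be reported as the primary result. The deciding comparison could then be chosen after the data are seen.

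Two things are at stake. The false-positive rate of the primary claim is not fixed at the 5% used for sizing. The planned power also refers to no identified comparison.

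This is not simply detail left to an analysis plan. The article does not leave the time point open; it names three. An analysis plan that later picked one would be changing the stated primary outcome.

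**Working it through.** **Inputs from the protocol article.** Three post-baseline visits (Primary outcome); alpha 0.05 two-sided, difference 8.5, SDs of change 5 and 13, 29 per group, 10% dropout, 62 in total (Sample size); 1:1 allocation (Randomization and allocation); general level 0.05 (Statistical analysis).

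**Assumed input.** The correlation of HRSD change between visits, which the article does not give. I show a range. One reference point: if raw scores have equal variance and a common correlation r at all visits, two changes from the same baseline have covariance proportional to 1 − r and variance proportional to 2(1 − r). Their correlation is therefore 0.5.

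**Step 1: the plan's own figure.** n = (z for alpha + z for power)² × (SD₁² + SD₂²) / difference². With the printed quantiles: (1.96 + 1.28)² × (25 + 169) / 8.5² = 10.4976 × 194 / 72.25 = 28.19, so 29 per group. The article prints 28.48, which rounds up to the same 29. The calculation contains one comparison at one alpha and makes no allowance for several visits.

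(The quantile 1.28 corresponds to 90% power; the stated 80% would give 21.08, so 22. That is a separate matter and this point does not rest on it.)

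**Step 2: error rate if any visit may count.** Independent tests: 1 − 0.95³ = 14.3%. For correlated tests, three standard normal statistics were simulated with 2 million draws, counting how often at least one exceeds 1.96 in absolute value:

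| Common correlation | Chance of at least one false positive |
|---|---|
| 0.3 | 13.6% |
| 0.5 | 12.5% |
| 0.7 | 10.9% |
| 0.8 | 9.8% |
| 0.9 | 8.4% |
| 0.95 | 7.4% |

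If correlation instead decays with distance between visits (first-order autoregressive, 0.5 to 0.9), the range is 12.9% to 8.8%. Over common correlations of 0.5 to 0.9 the rate is 12.5/5 = 2.5 to 8.4/5 = 1.7 times nominal. The interaction test is not counted.

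**Step 3: error rate if one contrast is fixed.** A single pre-named test, whether one visit or the overall group effect of the repeated-measures model, has a 5% error rate by construction.

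**Step 4: does a remedy need more patients?**
- One named contrast: the calculation in Step 1 is unchanged, provided its inputs apply to that contrast.
- All three visits kept at 0.05/3 = 0.0167 each: the same formula gives 28.11, so 29 per group at 80% power.
- Power per visit at 0.0167, normal approximation: 81.4% with 29 per group, and 79.8% with 28 (62 × 0.9 / 2 = 27.9).
- The same with a Welch t calculation: 77.7% and 75.8%, slightly under target.

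**The case against.** The best defence is the longitudinal reading. A multi-visit outcome, a repeated-measures ANCOVA, and maximum likelihood reserved for the primary outcome (last observation carried forward is for the secondary ones) fit together as one model of HRSD over time. Its overall group term would be a single 5% test. The article also does not say that visits are to be tested separately, and a condensed article may leave multiplicity rules to an analysis plan.

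Part of this stands. It shows that inflation is not inevitable and that a one-test solution is close at hand. It does not close the gap. The model is never designated as primary, it produces a group term and an interaction term, the two-sample tests stand beside it, and the sample size is a two-sample calculation on one change score.

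A reader might infer three stronger things that the article does not support:

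- **The error rate is doubled.** That needs an any-visit success rule, which the text permits but does not state, and a common correlation near 0.7 to 0.8, which is an assumption.
- **Requiring all three visits would cost the trial its power.** With the full 8.5-point effect and the same SDs assumed at every visit, that power at 28 per arm is about 78% to 82% (correlation 0.5 to 0.8). This is close to the stated 80% and shows no harm.
- **Week 4 is already the implied primary visit.** The hypothesis that mentions 4 weeks describes improvement under EA, not a comparison with sham, and nothing ties the 8.5 points to week 4.

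**Conclusion.** The point holds in conditional form. The article makes three visits primary and names no deciding visit, contrast or test and no error control, while the trial is sized on one comparison at two-sided 5%. If significance at any visit may be declared a primary success, the false-positive rate can reach about 8–13% for assumed correlations of 0.9 down to 0.5, and 14% under independence. It is 5% only if one contrast is fixed beforehand.

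The absence of a defined deciding comparison can be read directly from the text. The size of the inflation depends on the any-visit rule and on the assumed correlation. The sample size is not called into question by this point.

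**What to change.** Amend the protocol, with a date before unblinding, to:

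1. Name one primary between-group contrast and one test at two-sided 0.05. Two candidates are the HRSD change from baseline to week 4 (the end of the 12 sessions) estimated from the repeated-measures model, and that model's overall group effect. The choice is the sponsor's; what matters is that it is made in advance.
2. Make the remaining visits secondary, or keep them in the confirmatory set with a fixed testing order or an adjusted alpha.
3. State which visit the 8.5-point difference and the pilot SDs refer to, so that it is clear whether the sample size calculation applies to the chosen contrast.

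The cost is a formal amendment while recruitment is under way, and significance at another visit alone could no longer be called a primary success. With one named contrast the sample size need not change. Splitting alpha equally over three visits would leave power per visit at or a little below 80%, which favours a single contrast or a fixed order.

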##### Hamilton Rating Scale for Depression

The HRSD, originally published by Max Hamilton [24], is a multiple-item questionnaire that can provide an indication of depression and act as a guide for evaluating recovery. It is designed to assess depression severity by probing mood, feelings of guilt, suicidal ideation, insomnia, agitation or retardation, anxiety, weight loss, and somatic symptoms. The participants will be rated along 24 dimensions with scoring on a 3- or 5-point scale. A score of 0–7 is considered to be normal, and scores of 20 or higher indicate moderate, severe, or very severe depression. The assessment time is around 20 minutes [25]. The HRSD, evaluated by the researcher to assess the degree of depression of patients with PSD, can give an objective and reflective outcome.

#### Secondary outcomes

Secondary outcomes include the Zung Self-Rating Depression Scale (SDS), National Institutes of Health Stroke Scale (NIHSS), Barthel Index of Activities of Daily Living (BI), and Depression Scale of traditional Chinese medicine (Depression Scale of TCM), all of which will be evaluated at the same time points as the assessment of the primary outcome.

##### Zung Self-Rating Depression Scale

Designed by Duke University psychiatrist William W. K. Zung [26], the SDS is intended to assess the level of depression of patients who have been diagnosed with depressive disorder. A short self-rated questionnaire, it consists of 30 items that rate the affective, psychological, and somatic symptoms closely related to depression. Each question is scored on a scale of 1 through 4 based on responses “*a little of the time,” “some of the time,” “good part of the time,” and “most of the time*.” Scores fall into four ranges as follows: 20–44 indicates normal, 45–59 indicates mildly depressed, 60–69 manifests moderately depressed, and 70 and above defines severely depressed [27]. The SDS, assessed by patients with PSD themselves, can present a subjective and direct outcome.

##### National Institutes of Health Stroke Scale

The NIHSS, including domains such as level of consciousness, eye movements, visual fields, facial movements, muscle strength, sensation, coordination, language, speech, and neglect, is a 15-item scale used to measure neurological deficits and impairments caused by stroke. Each impairment is scored on a scale ranging from 0 to 2, 0 to 3, or 0 to 4. Scores are summed to range from 0 to 42. The higher the score, the more severe the neurological deficit [28].

##### Barthel Index of Activities of Daily Living

The BI is a scale considered to measure performance in activities of daily living, and each item is rated on the scale with a given number of points for each level [29]. Ten variables are used to describe activities of daily living and mobility. The BI has been used mainly to monitor functional outcomes related to stroke. A higher number indicates a greater likelihood of stroke patients living at home with a degree of independence after leaving the hospital.

##### Depression Scale of traditional Chinese medicine

To evaluate the degree of liver qi stagnation in the participants, the Depression Scale of TCM consists of six items concerning symptoms such as chest distress, belching, palpitation, insomnia, fatigue, irritability, and weeping. Each item is scored on a scale ranging from 0 to 3. Lower score sums manifest a slighter degree of liver qi stagnation. The Depression Scale of TCM, intended to reveal the exact TCM syndrome of depression, can be used to evaluate the EA treatment outcome of PSD from the perspective of TCM.

### Safety assessment

Participants’ safety will be evaluated during the whole EA treatment to avoid AEs, including local bleeding or pain at the acupuncture points, local redness or bruising, itching, and dizziness during treatment. At each visit, the time of occurrence, severity, progress, and treatment of AEs will be recorded in detail. If any serious AE occurs, the principal investigator and the institutional review board will be informed immediately, and direct actions will be taken right away.

### Sample size

According to the difference of HRSD scores between the two groups, the required sample size of each group will be carefully calculated by the data statistician. Based on our previous pilot study, the change in the SD of HRSD scores in the sham EA group is 5 points and that in the EA group is 13 points. If the HRSD score change in the EA group is 8.5 points higher than that in the sham EA group, it will be considered clinically significant. On the basis of a 5% false-positive error rate (α = 0.05, two-sided) and 80% power (β = 0.2), the sample size is estimated as follows:$$ {\displaystyle \begin{array}{l}n=\frac{{\left({Z}_{1-\alpha }+{Z}_{1-\beta}\right)}^2\times \left({\sigma}_1^2+{\sigma}_2^2\right)}{\delta^2}\\ {}\kern1.5em =\frac{{\left(1.96+1.28\right)}^2\times \left({5}^2+{13}^2\right)}{8.5^2}\approx 28.48\end{array}} $$

A sample size of at least 29 participants should be recruited in each group. Assuming about a 10% dropout rate, which has been verified in the pilot study, a total of 62 participants will be enrolled in the trial.

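### The variability figures of 5 and 13 are worded as a change in the SD but used as the SD of the HRSD change, so the stated 80% power cannot be confirmed

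*Protocol article*

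**What the plan says.** The Sample size section of the protocol article takes its variability input from pilot data: "the change in the SD of HRSD scores in the sham EA group is 5 points and that in the EA group is 13 points". The target difference is stated separately and as a difference in change: "If the HRSD score change in the EA group is 8.5 points higher than that in the sham EA group". The error rates are given as "On the basis of a 5% false-positive error rate (α = 0.05, two-sided) and 80% power (β = 0.2"). The printed formula is (Z₁₋α + Z₁₋β)² × (σ₁² + σ₂²) / δ², filled in as (1.96 + 1.28)² × (5² + 13²) / 8.5², with a printed result of 28.48. From this the section concludes: "A sample size of at least 29 participants should be recruited in each group". It then adds: "Assuming about a 10% dropout rate, which has been verified in the pilot study, a total of 62 participants will be enrolled in the trial". Allocation is 1:1 (Randomization and allocation), and the primary outcome is the change in HRSD score (Primary outcome). The article gives no pilot mean change, pilot size or pilot time point, and no other SD.

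**The concern.** Both the endpoint and δ are changes in HRSD, so σ₁ and σ₂ must be the SDs of the HRSD change in each arm. The sentence describes a different quantity: how much an SD changed. The key input is therefore defined as something the formula cannot use, and nothing else in the article lets a reader recover the right one.

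Two features make it reasonable to ask whether 5 and 13 are SDs at all:

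- Their difference is 8, next to the chosen δ of 8.5, which is what one would expect if they were pilot mean changes.
- As SDs they would differ 2.6-fold between two randomised arms on the same scale, which is unusual.

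These two figures and δ fix the size of the trial. If 5 and 13 are not SDs, neither 29 per arm nor 62 in total rests on any estimate of variability.

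**Working it through.** **Inputs (Sample size section).** δ = 8.5; 5 (sham EA) and 13 (EA), used as σ; two-sided α = 0.05, z = 1.96; stated power 80%, for which z = 0.84; z actually printed, 1.28, which belongs to 90%.

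**1. The plan's own figure.** (1.96 + 1.28)² × (25 + 169) / 72.25 = 10.4976 × 194 / 72.25 = 28.19. The article prints 28.48. Both round up to 29, so the small difference has no effect. The 29 is thus reproduced, but only with the 90% value of z.

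**2. The same formula at the stated power.** (1.96 + 0.84)² × 194 / 72.25 = 7.84 × 194 / 72.25 = 21.05, or 22 per arm. Under a Welch t test, 22 per arm gives 78.8% and 23 gives 80.7%, so about 22 is a fair summary.

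**3. Number per arm to judge.** Either the 29 that the article asks for, or what remains of 62 after 10% loss: 62 × 0.9 / 2 = 27.9, about 28.

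**4. Reading A: 5 and 13 are SDs of the change.** The standard error of the difference is √(194/n), which is 2.632 at n = 28 and 2.586 at n = 29. The ratio of δ to the standard error is 3.23 and 3.29.

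| n per arm | Normal approximation | Welch t |
|---|---|---|
| 28 | 89.8% | 88.1% |
| 29 | 90.8% | 89.2% |

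**5. Reading B: they are not SDs of the change.** The article then offers no SD. The common SDs below are assumptions, chosen only to show the range; δ = 8.5, two-sided 5%, noncentral t.

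| Assumed common SD of change | Power at 28 per arm | Power at 29 per arm |
|---|---|---|
| 8 | 97% | 98% |
| 10 | 88% | 89% |
| 13 | 67% | 69% |

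The largest common SD that still gives 80% is about 11.1 at 28 per arm and 11.4 at 29, so about 11.3. The normal approximation, SD = 8.5 × √(n/2) / 2.80, gives about 11.4 and 11.6.

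**6. Hints that the figures might be means.** 13 − 5 = 8, against δ = 8.5. 13 / 5 = 2.6 as a ratio of SDs, or 169 / 25 = 6.8 as a ratio of variances.

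**The case against.** The strongest reply is that this is a word-order slip for the SD of the change. The formula labels 5 and 13 as σ, squares and adds them, and states δ separately; it also allows unequal spread by design, and pilot SDs can be unstable. On that reading power is above 80%, not below it. This stands as a plausible reading, and it rules out any claim that the trial is shown to be underpowered. It does not rescue the stated power: the same reading gives about 88–89%, because the z value and the stated power disagree.

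A reader might infer that 5 and 13 are mislabelled mean changes. The document does not establish that. No pilot means are given, 8 is not 8.5, and the article presents 8.5 as a threshold of clinical relevance, not as the pilot difference.

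A reader might also argue that an SD of 13 is implausible given the HRSD entry range of 8 to 35. That range limits scores at entry, not later scores or changes. Arguments from the share of patients who would worsen, or improve beyond their starting score, would need a normal distribution, a baseline value and a mean change in the EA arm, none of which the article supplies.

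Finally, a condensed article may leave pilot details to the full protocol. That is fair for the pilot's size and design. It does not cover a calculation that is printed in full with its main input wrongly described.

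**Conclusion.** The point holds as a defect of definition. The input as worded is not the quantity the formula needs, and the article does not settle what it is.

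The stated 80% fails to match the calculation on the favourable reading (about 88–89%) and has no basis on the other. In that second case the power depends on an unknown SD and meets 80% only up to a common SD of about 11.3. The 67–69% figure requires an SD of 13 in both arms, which is an assumption and appears nowhere in the article.

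Neither mislabelled means nor a shortfall in power is shown. What is shown is that the figure must be restated on either reading.

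**What to change.** Return to the pilot data and establish what 5 and 13 are. State the SD of the HRSD change in each arm, with the mean change, so that the two cannot be confused. Re-run the formula with those SDs and with the z value that matches the stated power: 0.84 for 80%, or 1.28 with the text changed to 90%. Then restate the power that the 62 patients give, over a plausible range of SDs if the pilot estimate is uncertain, without changing enrolment.

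The cost is a look at existing pilot data and one rewritten paragraph. The restated power may prove higher or lower than 80%. If 5 and 13 turn out to be SDs of the change, only the wording and the power statement need correcting.

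### The sample-size formula uses z = 1.28, the value for 90% power, although the text states 80% power (β = 0.2)

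*Protocol article*

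**What the plan says.** Everything needed is in the Sample size section of the protocol article, apart from the allocation ratio.

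- Error rates: "On the basis of a 5% false-positive error rate (α = 0.05, two-sided"), followed by "and 80% power (β = 0.2), the sample size is estimated as follows".
- Variability, taken from pilot data: "the change in the SD of HRSD scores in the sham EA group is 5 points and that in the EA group is 13 points".
- Target difference: "If the HRSD score change in the EA group is 8.5 points higher than that in the sham EA group", this is to count as clinically significant.
- Formula: the squared sum of Z(1−α) and Z(1−β), times the sum of the two variances, divided by the squared difference. The numbers inserted are 1.96 and 1.28, 5² and 13², and 8.5². The printed result is about 28.48.
- Conclusion: "A sample size of at least 29 participants should be recruited in each group".
- Dropout: "Assuming about a 10% dropout rate, which has been verified in the pilot study, a total of 62 participants will be enrolled".

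The Randomization and allocation section sets equal allocation ("in a 1:1 ratio after they have signed printed informed consent forms"). No other section states a power or explains the 1.28.

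**The concern.** The term labelled Z(1−β) must be the normal quantile of the stated power. For β = 0.2 it is 0.84; the value inserted, 1.28, belongs to β = 0.10. One paragraph thus states one power and calculates with another.

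This is the only power statement in the article, and it rests on HRSD change, the primary outcome. α, power, target difference and n should reproduce one another. Here a reader who starts from the stated β arrives at 22 per group, and a reader who starts from the 29 arrives at about 90% power. The stated risk of missing a true 8.5-point difference (20%) is about twice what the design carries on its own inputs (about 10%), so a reader would take the trial to be less informative than planned. It also stays unclear whether the trial was designed for 90% power with a misprinted β, or for 80% with the wrong quantile and seven more patients per group than needed.

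Three smaller slips sit in the same paragraph. The printed 28.48 is not the value of the printed expression. The symbol Z(1−α) does not match 1.96, which is Z(1−α/2). And the pilot SDs are described as a change in the SD, whereas the formula needs the SD of the change.

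**Working it through.** **Inputs** (Sample size section; allocation from Randomization and allocation): two-sided α = 0.05, so z = 1.96; stated power 80%; SDs 5 and 13, so the variances sum to 25 + 169 = 194; difference 8.5, squared 72.25; allocation 1:1.

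**Formula:** n per group = (z_α + z_β)² × (σ₁² + σ₂²) / δ².

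**1. The article's own substitution.** (1.96 + 1.28)² × 194 / 72.25 = 10.4976 × 194 / 72.25 = 28.19, rounded up to 29. The 29 reproduces; the printed 28.48 does not. Exact quantiles for two-sided 5% and 90% power give 28.21, so rounding of z does not explain it. To obtain 28.48 the second z would have to be 1.297.

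**2. Which power 1.28 stands for.** Φ(1.28) = 0.8997, that is 90%.

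**3. The stated 80% power.** (1.96 + 0.84)² × 194 / 72.25 = 7.84 × 194 / 72.25 = 21.05 (21.08 with exact quantiles), so 22 per group. With a Welch t test, power is 78.8% at 22 and 80.7% at 23, so 23 per group.

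**4. Whether another standard reading rescues 29.** One-sided α = 0.05 gives 16.6 (17 per group) at 80% power and 22.99 (23 per group) at 90%. Neither gives 29.

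**5. Power at 29 per group.** The standard error of the difference is √(194/29) = 2.586, and 8.5 / 2.586 = 3.286.

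- Normal approximation: Φ(3.286 − 1.96) = Φ(1.326) = 90.8%.
- Welch t, noncentrality 3.286, df = 28 × 194² / (25² + 169²) = 36.1: 89.2%.
- Pooled t, 56 df: 89.8%.

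**6. Difference detectable with 80% power at 29 per group.** (1.96 + 0.84) × 2.586 = 7.24, so about 7.2 points rather than 8.5.

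**7. After the assumed dropout.** 62 × 0.9 = 55.8, about 28 per group.

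| Per group | Normal approximation | Welch t |
|---|---|---|
| 22 | 81.7% | 78.8% |
| 28 | 89.8% | 88.1% |
| 29 | 90.8% | 89.2% |
| 31 | 92.5% | 91.2% |

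At every size from the number left after dropout (28) to full enrolment (31), the power is well above 80%.

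**The case against.** The contradiction itself cannot be argued away: 1.28 is the value that produces the stated 29, so it is not a fault of text extraction. The case on the other side concerns weight and remedy.

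- **The error is conservative.** If 80% is read as a minimum, it is met with room to spare, and neither patients nor validity are at risk from this mismatch. That stands. It limits the harm, but the stated power is still not the power of the stated n.
- **The effect on reading a null result is partly speculative.** Such a result is read mainly from its confidence interval, and the Statistical analysis section plans 95% intervals. Moreover, the figure near 90% belongs to a single two-sample comparison with the pilot SDs, while the primary outcome covers several visits and a repeated-measures analysis is also planned. This stands as a qualification: 90% is the power of the printed calculation, not a guarantee for every planned analysis. The stated 80% rests on that same calculation.
- **The article does not show which figure is wrong.** This also stands. Restating 90% is the repair that leaves 1.28, 29 and 62 in place, but the sponsor has to confirm it.
- **Keeping 62 ignores dropout.** If 29 evaluable per group is a strict minimum, a 10% loss calls for 29 / 0.9 = 32.2, so 33 per group or 66 in total; 62 tolerates only (62 − 58) / 62 = 6.5% loss. That arithmetic is right, but the consequence is small: at 28 per group the power is 89.8% (normal) or 88.1% (Welch), so a statement of about 90% still holds.
- **The side slips change nothing.** Both 28.19 and 28.48 round up to 29, and the Z(1−α) label is notation only, since the text says two-sided. True; they are worth correcting only because the paragraph has to be rewritten anyway.

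**Conclusion.** The concern holds. The paragraph states 80% power and calculates with the quantile for 90%. On its own inputs, 29 per group gives about 90% power (90.8% normal, 89.2% Welch) and 80% power needs 22 per group (23 with a Welch t test), so the stated power is about 10 percentage points too low for the stated n. The printed 28.48 should be 28.19.

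These figures assume the pilot SDs of 5 and 13, a true difference of 8.5 points, equal groups and one two-sided comparison at 5%. The error runs in the safe direction and does not leave the trial underpowered. It should nevertheless be corrected before results are reported, because it affects the only power statement in the article.

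**What to change.** In the Sample size section:

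1. Have the sponsor confirm from the planning records which power was intended.
2. If 90% was intended, state 90% power (β = 0.10), keep 1.28, write Z(1−α/2) in place of Z(1−α), and correct the result to 28.19, so 29 per group.
3. If 80% was intended, insert 0.84, report 21.05 and 22 per group, and say that the planned 29 exceeds this and gives about 90% power.
4. In either case, add that 29 per group has 80% power for a difference of about 7.2 points, and describe the 5 and 13 as SDs of the change in HRSD score.
5. Note that 62 enrolled with 10% loss leaves about 28 per group, slightly under 29, with power of 88% to 90% on the same inputs.

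The cost is rewording one paragraph. This correction needs no extra patients and no change to the analysis.
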